# Design of a randomised acupuncture trial on functional neck/shoulder stiffness with two placebo controls

**DOI:** 10.1186/1472-6882-14-246

**Published:** 2014-07-16

**Keywords:** Acupuncture, Placebo, Neck stiffness, Shoulder stiffness, Double-blind, Randomised, placebo-controlled trial

## Abstract

**Background:**

Functional neck/shoulder stiffness is one of the most well-known indications for acupuncture treatment in Japan. There is little evidence for the effectiveness of acupuncture treatment for functional neck/shoulder stiffness. Research using two different placebos may allow an efficient method to tease apart the components of real acupuncture from various kinds of ‘non-specific’ effects such as ritual with touch or ritual alone. Herein, we describe a protocol of an ongoing, single-centre, randomised, placebo-controlled trial which aims to assess whether, in functional neck/shoulder stiffness, acupuncture treatment with skin piercing has a specific effect over two types of placebo: skin-touching plus ritual or ritual alone.

**Methods:**

Six acupuncturists and 400 patients with functional neck/shoulder stiffness are randomly assigned to four treatment groups: genuine acupuncture penetrating the skin, skin-touch placebo or no-touch placebo needles in a double-blind manner (practitioner-patient blinding) or no-treatment control group. Each acupuncturist applies a needle to each of four acupoints (Bladder10, Small Intestine14, Gallbladder21 and Bladder42) in the neck/shoulder to 50 patients. Before, immediately after and 24 hours after the treatment, patients are asked about the intensity of their neck/shoulder stiffness. After the treatment, practitioners and patients are asked to guess whether the treatment is “penetrating”, “skin-touch” or “no-touch” or to record “cannot identify the treatment”.

**Discussion:**

In addition to intention-to-treat analysis, we will conduct subgroup analysis based on practitioners’ or patients’ guesses to discuss the efficacy and effectiveness of treatments with skin piercing and various placebo controls. The results of practitioner and patient blinding will be discussed. We believe this study will further distinguish the role of different components of acupuncture.

**Trial registration:**

Current Controlled Trial ISRCTN76896018

## Background

Functional neck/shoulder stiffness is the second most frequent subjective symptom next to lumbago [1] and one of the most well-known indications for acupuncture treatment in Japan. Functional neck/shoulder stiffness refers to discomfort, tightness or rigidity in the muscles supporting the neck [2,3], without any specific diseases that cause such complaints. In routine clinical care with acupuncture, patients well experience that needle penetration at acupoints effectively reduces tension and discomfort in the neck and shoulder. The mechanisms underlying the effectiveness of acupuncture for functional neck/shoulder stiffness are unclear. Stiffness and its resultant discomfort in the muscles might be mitigated through neuronal circuits that are similar to those to modulate pain and its resultant unpleasantness [4,5], through the improvement of regional blood circulation [6,7] or through the suppression of moto-neuron activity that innervates the stiff muscles [8]. Some have argued that acupuncture is primarily a placebo effect [9]. There is little evidence for the efficacy of acupuncture treatment for functional neck/shoulder stiffness, and no randomised, placebo-controlled trials (RCTs) investigating acupuncture under double-blind (practitioner-patient) conditions has been reported.

Single-blind RCTs using single-blind acupuncture placebo/sham devices have been considered the most rigorous method for investigating the efficacy of acupuncture [10-13]. However, single-blind design has the potential to produce biases from unmasked practitioners, and evidence obtained under single-blind conditions is arguably insufficiently rigorous [14-21]. Practitioner blinding has been absent in acupuncture research and it may be crucial in acupuncture research to meet the gold standard of double-blind RCTs whereby the specific effects of interventions can be distinguished under double-blinding conditions from non-specific effects [22]. In acupuncture research, however, the gold standard was considered almost impossible to achieve because blinding an acupuncturist is very difficult due to the nature of the procedure [10-15]. To solve this methodological difficulty, we designed two types of non-penetrating placebo needles: one where the tip touches the skin (skin-touch placebo needles), and another where the needle tip does not reach the skin (no-touch placebo needles). We also designed a matched genuine penetrating acupuncture needle. We have evaluated them for use in clinical settings [23-29]. In this study beside genuine penetrating acupuncture we will have two placebo acupuncture controls and an additional no-treatment control. Our two placebos will allow disentanglement to what extent skin-touching plus ritual or ritual alone contributes to the non-specific effects of placebo acupuncture and allow for a precise estimate of the mechanism whereby acupuncture may work in clinical practice.

In this study, we enrol patients who had functional neck/shoulder stiffness not due to any specific disease. To determine the efficacy of acupuncture for neck/shoulder stiffness, we use the three types of aforementioned needles to perform a randomised, double-blind (practitioner-patient), placebo-controlled study. The primary aims of the present study are to assess whether acupuncture treatment with skin piercing is superior to two different placebo treatments one with skin-touching plus ritual and one with ritual alone under double-blind conditions. The two placebo controls will allow for a more precise estimate of the components of acupuncture treatment, what might be a superior placebo. The no-treatment control will allow a determination as to whether any of the treatments are superior to natural progression, spontaneous remission or regression to the mean.

## Methods

This ongoing study started from January 2011 and will complete in March 2015. The study protocol was approved by the Ethics Committee of Tokyo Ariake University of Medical and Health Sciences. The study protocol followed CONSORT recommendations. The trial has been registered with the ISRCTN76896018
[30].

### The acupuncture needles

We use three types of needles sterilized with gaseous ethylene oxide for a double-blind study design: 1) penetrating needles that can pierce the skin; 2) skin-touch placebo needles, the tip of which can touch against the skin but cannot penetrate it; 3) no-touch placebo needles, the tip of which cannot reach the skin. The appearances of these three types of needles are indistinguishable. The diameter of the needles is 0.18 mm. The insertion depth of the penetrating needle is 5 mm. A pedestal is used for the needles. These needles developed for the research employing Japanese style acupuncture have been described in detail elsewhere [23-29,31].

### Study design

This is a randomised, double-blind (practitioner-patient blinding), placebo-controlled study performed in a single centre including four arms: treatment with penetrating needles (penetrating treatment), treatment with skin-touch placebo needles (skin-touch placebo treatment), treatment with no-touch placebo needles (no-touch placebo treatment) and control with no treatment (no-treatment control) [23-29].

### Setting and participants

The study is conducting at Japan School of Acupuncture, Moxibustion and Physiotherapy, and Tokyo Ariake University of Medical and Health Sciences, Tokyo, Japan.

We employ six (three males, three females) experienced and licensed acupuncturists, and recruit 400 volunteers with functional neck/shoulder stiffness who are students, teachers and staff at the Japan School of Acupuncture, Moxibustion and Physiotherapy or Tokyo Ariake University of Medical and Health Sciences. The aim and details of this study are fully explained to each practitioner and patient using a written consent form. All participants sign written consent form before each treatment starts.

### Interview to exclude volunteers

Before patients enter this study, an assistant interviews volunteers using an interview sheet to record basic demographics and to exclude volunteers who do not meet the inclusion criteria of this study. After the interview sheet is filled out, the assistant measures the patient’s blood pressure and then the assistant checks for any omissions. The assistant says the same words in the same tone to every patient and remain blinded from the nature of the needles throughout the experiment.

#### Inclusion criteria

1. Patients are 18 to 60 years old.

2. Patients have functional neck/shoulder stiffness without pain.

3. Patients have experienced receiving acupuncture and have experienced de-qi.

#### Exclusion criteria

1. Patients have a plan within 24 hours to receive acupuncture, massage, medication or any other treatment for neck/shoulder stiffness.

2. Patients have a plan within 24 hours to do self-care for neck/shoulder stiffness, e.g., exercise, stretching and/or supplements.

3. Patients have been diagnosed with any of the following diseases: cervical spondylosis; cervical hernia of the intervertebral disk; cervicobrachial disorder; thoracic outlet syndrome; hepato-cholecystopathy; high blood pressure; cerebrovascular disease; cardiac disease.

4. Patients have any neurological symptoms, such as paralysis or numbness in the neck, shoulder or upper extremities.

5. Patients diagnosed they had diseases to produce neck/shoulder stiffness according to the last annual medical examination.

6. Systolic blood pressure is over 140 mmHg and/or diastolic pressure is over 90 mmHg just before the treatment.

### Randomisation

After screening, qualified patients are randomly assigned to one of the four arms (Figure 1).

**Figure 1 F1:**
[figure not shown]
Trial flow diagram.

Before the trial, we prepared 100 sets of four genuine acupuncture needles for penetrating treatment, 100 sets of four skin-touch placebo needles for skin-touch placebo treatment and 100 sets of four no-touch placebo needles for no-touch placebo treatment. The 400 bags for sterilisation numbered from 1 to 400 were randomly assigned to the penetrating, skin-touch placebo, no-touch placebo, or no-treatment control arm using a table of random numbers that was generated by the RAND function (Microsoft Excel 2003). Four penetrating needles, four skin-touch placebo needles or four no-touch placebo needles were put in a numbered bag corresponding to the assigned treatment type and sealed by the study controller; then they were sterilised with ethylene oxide gas.

The first to the last patient in order are each assigned one of the 400 numbered bags. As a result, 400 patients are randomly assigned to penetrating, skin-touch placebo, no-touch placebo treatment or no-treatment control. Each of the six acupuncturists treats 50 patients consecutively and in order.

### Explanation to patients

At the beginning of the study, each patient is informed the following: “You are going to be randomly assigned to one of the four groups: acupuncture with needles that penetrate the skin, acupuncture with needles that touch the skin but cannot penetrate the skin, acupuncture with needles that cannot reach the skin, or no-treatment control sitting in a massage chair without acupuncture treatment. In case you are assigned to the no-treatment control group, we will treat your stiffness in the neck/shoulder using real needles after completion of the trial if you desire. You have a one-fourth chance of being assigned to the no-treatment control group. The needles are designed to be less painful, so you may not feel pain from treatment”.

### Patients’ evaluation of neck/shoulder stiffness before treatment

Before patients’ evaluation, the assistant makes sure the patients fully understand and that they evaluate the amount of neck/shoulder stiffness only on the right or left side whichever the patients feel is more severe.

The patients record where the strongest stiffness is on the figure in which neck and shoulder is drawn and its duration they have (less than 2 weeks, 2 weeks to 3 months, more than 3 months). The patients rate the intensity of neck/shoulder stiffness by a verbal rating scale (VRS: none, weak, moderate, strong, very strong) and on a 100 mm visual analogue scale (VAS) ranging from 0 (no neck/shoulder stiffness) to 100 (the most severe neck/shoulder stiffness imaginable). The unilateral neck/shoulder in which the patients have stiffness or feel more stiffness than the other side is decided to treat before treatment.

### Needle application and acupoints

Then, the assistant asks the patients to sit on a massage chair, to relax and not to touch or press their own body, especially the neck and shoulder. The patients are asked to indicate the place with the most severe stiffness in the neck/shoulder without touching when the acupuncturist asks them about it.

The assistant tells the acupuncturist that a patient is ready to receive treatment. The acupuncturist enters a treatment booth after an assistant’s signal and she says the following: “Hello, I am going to treat your neck/shoulder stiffness from now on. Please point to where you have the strongest stiffness in the neck or shoulder”. The acupuncturist confirms it and marks the point where the patient indicates. Excluding one of the acupoints BL(Bladder)10, GB(Gallbladder)21, SI(Small Intestine)14 and BL42 in the neck or shoulder (Figure 2) [32], whichever is nearest to the most severe stiffness, the other three acupoints are located and marked to apply needles with a light touch. These acupoints are where many patients with neck/shoulder stiffness complain and commonly used for the treatment of neck/shoulder stiffness.

**Figure 2 F2:**
[figure not shown]
Acupoints for treatment used in this trial.

The acupuncturist says “I am going to start acupuncture treatment and sterilise the skin with alcohol at and around the acupoints” and sterilises the skin on which the acupoint is located.The assistant prepares a set of four needles, spirits-of-wine cotton and fingerstall, and sets each needle assembly into an extra guide tube (Figure 3). The assistant peels off the seal of the pedestal of each needle and hands the needle to the acupuncturist just before each needle application.

**Figure 3 F3:**
[figure not shown]
**Double-blind needle assembly and extra guide tube. A**: Extra guide tube. Diameter of upper part of extra guide tube is smaller than that of guide tube needle assembly. **B**: Needle assembly. **C**: Needle assembly covered with extra guide tube. **(a)** indicates insertion depth with tapping-in method. **(b)** indicates whole insertion depth.

Before each needle application, the acupuncturist massages the skin at and around each acupoint with the pulp of index finger with fingerstall (pre-massage). The massage is very light and entails three small strokes. The acupuncturist places a needle on an acupoint, and makes “holding hand” to fix the entire needle assembly with the non-dominant hand (Figure 4A); then with the index finger of the dominant hand, he/she taps the upper end of the needle handle protruding from the top of the extra guide tube to penetrate the skin or the lower stuff in skin-touch and no-touch placebo needles (tapping-in method) (Figure 4B) [29]. After tapping-in method, the acupuncturist removes the extra guide tube (Figure 4C) to insert the needle further by rotating the needle clockwise and counterclockwise alternately (alternating twirling technique) (Figure 4D) [23-28]. Each needle is inserted until the needle tip reaches the target depth, and then the needle is rotated three times.

**Figure 4 F4:**
[figure not shown]
**Course of needle application using extra guide tube in this study. A**: Needle assembly covered with extra guide tube is placed on acupoint. **B**: Upper end of needle handle is tapped (tapping-in method) to penetrate skin. **C**: Extra guide tube is removed from needle assembly after tapping-in method. **D**: Needle is inserted with alternating twirling technique.

For each treatment, the acupuncturist applies one needle to BL10, GB21, SI14 and BL42 in that order on the side with the most stiffness. After all four needles are applied, the acupuncturist says to the patient “The needles are going to remain in the body for 10 min (10 min retention)”, and leaves the treatment booth. The assistant says “Please refrain from moving the neck, shoulder or hand. If you feel unbearable pain or something uncomfortable, please let me know. Please relax and do not force yourself to stay awake”.

Ten minutes later, the acupuncturist comes into the treatment booth and says “I am going to remove the needles now”. The acupuncturist returns the needle handle to its initial position by the alternating twirling technique [23-28], removes the entire needle assembly from the skin, and then puts it into an opaque envelope held by the assistant. After removal of each needle, the acupuncturist massages just like pre-massage the place where the needle is applied with three small strokes using the pulp of the index finger with fingerstall to prevent infection with bleeding (post-massage), and then sterilises that area. If there is bleeding, the acupuncturist presses sterilised cotton between the finger and the patient’s skin, and reports the incidence in a questionnaire for practitioners. The needles are removed in the same order in which they are applied.

After treatment is completed, the acupuncturist tells the patient “The acupuncture treatment is done”. Then, the acupuncturist leaves the treatment booth and answers a questionnaire for practitioners.

The assistant observes whether needling have any untoward effects, then asks the patient to dress. In the rare circumstance of slight external bleeding from a point of needle removal the assistant will apply pressure with sterilised cotton to stop bleeding. If there is any internal bleeding after needle removal, the assistant tells the patient that slight internal bleeding occurs and that it will disappear within several days.

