### Patients’ evaluation immediately after treatment

The patients rate the intensity of stiffness at the area of strongest stiffness immediately after the treatment by a VRS (none, weak, moderate, strong, very strong) and on a 100 mm VAS ranging from 0 (no neck/shoulder stiffness) to 100 (most severe neck/shoulder stiffness imaginable). Also the patients rate the change in stiffness in the area of strongest stiffness compare with before the treatment by a VRS (clearly worsen, slightly worsen, no changed, slightly improved, clearly improved). When they rate “clearly or slightly worsen”, they rate the change on a 100 mm VAS ranging from −100 (worsened to the most severe stiffness imaginable) to 0 (no change). When they rate “clearly or slightly improved”, they rated the change on a 100 mm VAS ranging from 0 (no change) to 100 (completely cured no stiffness). For the no-treatment control group, after the 10 min of no-treatment period the patients report the same items.

Excluding no-treatment control group, the patients report what they feel during the treatment. If they feel pain from the treatment, they rate pain intensity on a 100 mm VAS ranging from 0 (no pain) to 100 (most severe pain imaginable). If they feel de-qi from the treatment, they rate de-qi intensity on a 100 mm VAS ranging from 0 (no de-qi) to 100 (strongest de-qi imaginable). Further they rate their pleasantness or unpleasantness to the treatment on a 200 mm VAS ranging from −100 (very unpleasant) to 0 (neither pleasant nor unpleasant) to 100 (very pleasant), and rate their satisfaction with the treatment on a 200 mm VAS ranging from −100 (completely unsatisfied) to 0 (neither satisfied nor unsatisfied) to 100 (completely satisfied).

Then, the patients guess whether the treatment is “penetrating”, “skin-touch” or “no-touch” or to record “cannot identify the treatment” and they report their confidence level in their guesses by a VRS (with confidence, with slight confidence, with little confidence, with no confidence) and on a 100 mm VAS ranging from 0 (no confidence) to 100 (full assurance) [24,28,29].

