### Practitioners’ guess as to treatment

After completion of treatment with four needles, the acupuncturists guess whether the treatment is “penetrating”, “skin-touch” or “no-touch” or to record “cannot identify the treatment”; they report their confidence in their guesses by a VRS (with confidence, with slight confidence, with little confidence, with no confidence) and on a 100 mm VAS ranging from 0 (no confidence) to 100 (full assurance) [24,27-29]. Additionally, the acupuncturists indicate which clues influence their guesses, such as the patient’s expression, behaviour, external bleeding, internal bleeding, lack of bleeding, reaction to needle insertion, reaction to needle removal and other clues [24,27].

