### Outcomes

#### Primary measurements

Improvement of neck/shoulder stiffness score immediately and 24 hours after the treatment are primary outcomes.

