#### Secondary outcome measurements

Practitioners’ and patients’ guesses at treatments and their confidence in their guesses and, pain and de-qi felt during treatment by the patients are secondary outcomes.

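### As narrated, patients with internal bleeding are told of it before the immediate stiffness rating and guess, a strong allocation cue in one arm only

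*Protocol article*

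**What the plan says.** The relevant statements are spread over several Methods sections of the protocol article.

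- **Needle application and acupoints**, after removal: "The assistant observes whether needling have any untoward effects, then asks the patient to dress". If internal bleeding is found, "the assistant tells the patient that slight internal bleeding occurs and that it will disappear within several days".
- **Patients' evaluation immediately after treatment**, the next section: "The patients rate the intensity of stiffness at the area of strongest stiffness immediately after the treatment by a VRS" and on a 100 mm VAS. After ratings of change, pain, de-qi, pleasantness and satisfaction comes the guess: "Then, the patients guess whether the treatment is “penetrating”, “skin-touch” or “no-touch” or to record “cannot identify the treatment".
- **Primary measurements**: "Improvement of neck/shoulder stiffness score immediately and 24 hours after the treatment are primary outcomes". **Secondary outcome measurements** include "Practitioners’ and patients’ guesses at treatments and their confidence in their guesses".
- **The acupuncture needles**: one needle type pierces the skin, one touches it without penetrating, and one does not reach it. **Explanation to patients** tells every patient about all three.
- **Practitioners' guess as to treatment**: the clues a practitioner may name include "external bleeding, internal bleeding, lack of bleeding".
- **Interview to exclude volunteers**: the assistant is to speak identically to every patient and "remain blinded from the nature of the needles throughout the experiment".

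**The concern.** The message goes only to patients who bleed. By the protocol's own account of the needles, those patients should all be in the penetrating arm. The recipients can interpret it: they know that two needle types do not pierce, all have had acupuncture before, and they are students, teachers or staff of an acupuncture school or a health-sciences university. The protocol itself treats bleeding as information about allocation when it lists the practitioners' clues.

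Three things are at stake. The primary outcome is the patient's own rating, so belief about the arm can move it. The patient's guess, a secondary outcome, is taken after staff have supplied a clue. And the Discussion plans subgroup analyses by guess, to separate the effect of needling from the effect of recognising the treatment; recognition prompted by a staff member in one arm only blurs that separation.

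**Working it through.** The documents give no bleeding rate, SD, alpha or effect size for this point, so there is no stated figure to reproduce. The check is of sequence, with a calculation for scale only.

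**Sequence as narrated**

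1. The acupuncturist removes the needles, leaves the booth and fills in the practitioner questionnaire.
2. The assistant looks for untoward effects and has the patient dress. The care of external bleeding and the message about internal bleeding are described here.
3. The next section covers the immediate stiffness rating, the other ratings and the guess.
4. A later section covers the 24-hour stiffness rating and second guess.

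No sentence holds the message back until step 3 is finished, and none provides a matching message for needle-arm patients who do not bleed.

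**How informative is the message?** Let b be the share of penetrating patients told of bleeding and f the share in each placebo arm. With three equal needle arms of 100,

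P(penetrating | told) = b / (b + 2f).

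- The protocol's needle description implies f = 0, which gives 100%.
- If a placebo device could bruise (assumed f = 1%): b = 10% gives 0.10/0.12 = 83%, and b = 20% gives 0.20/0.22 = 91%.
- At the unfavourable corner examined (b = 5%, f = 2%): 0.05/0.09 = 56%, against one third without the message.

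**How far could the immediate comparison move?** Let d be the change in the VAS rating caused by being told. The shift in the penetrating-arm mean is b × d. With an assumed SD of 25 mm and 100 per arm, SE = 25 × √(2/100) = 3.54 mm. The last column is the rejection rate of a two-sided 5% z-test with no true effect.

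| b (assumed) | d (assumed) | shift b × d | rejection rate |
|---|---|---|---|
| 2% | 5 mm | 0.1 mm | 5.0% |
| 5% | 10 mm | 0.5 mm | 5.2% |
| 10% | 10 mm | 1.0 mm | 5.9% |
| 20% | 10 mm | 2.0 mm | 8.7% |
| 30% | 20 mm | 6.0 mm | 39.6% |

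The rejection rate is the same for either sign of d. The table shows what would have to be true for the shift to matter; it does not estimate the shift.

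**The case against.** **The order is inferred.** No sentence says that the message precedes the rating, and the rating is described as made immediately after treatment. This is a condensed article and the full script is not shown. That stands, so the point is limited to the procedure as narrated. The message is nevertheless tied to the post-removal check, and nothing points to a different order.

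**The message is not the only cue.** If a site bleeds at removal, the acupuncturist presses cotton on it while the assistant holds the envelope, and the assistant may apply pressure later. This stands too. The assistant learns of bleeding by seeing it, so changing when the patient is told cannot restore the assistant's blinding. What changing the order can protect is the patient's immediate rating and guess.

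**Size and direction are unknown.** A reader might infer that the message favours penetrating needles. The documents do not support that: belief in real needling could improve the rating, but news of bleeding in the treated area could worsen it. External bleeding is called rare, no rate is given for internal bleeding, and at 5-10% told with a 10 mm shift the rejection rate is only 5.2-5.9%. A negligible effect on the mean is therefore possible.

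**The leak is partly visible.** Patients guess twice, practitioners report bleeding and may name it as a clue, and blinding is to be discussed. These records can show unblinding, but they do not remove it from the ratings.

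**Conclusion.** The concern holds in a bounded form. As narrated, a message given only to patients with internal bleeding precedes a self-rated primary outcome and the guess. By the protocol's own needle description it marks the penetrating arm. It is at odds with the statement that the assistant uses the same words for everyone. That statement stands in the interview section and could be read as covering the interview alone, but the blinding clause beside it expressly runs throughout the experiment, and the sight of bleeding is hard to square with it.

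Two stronger readings go too far. One is that the message proves the arm: that depends on placebo devices never bruising, and otherwise it is a strong clue. The other is that the immediate comparison is known to be biased towards penetrating needles: neither sign nor size can be derived from the documents, and the 0.1-6.0 mm range rests wholly on assumed bleeding rates, rating shifts and SD. The case for acting is that the leak is one-sided, avoidable for the immediate measurements and cheap to close, in a trial whose central claim is practitioner-patient blinding.

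**What to change.** 1. Reconcile the assistant's instructions in Needle application and acupoints with those in Interview to exclude volunteers, and state explicitly the order of message, rating and guess.
2. Leave the care of bleeding and its disclosure as they are. For patients still to be treated, have the immediate stiffness ratings and the guess completed before the message is given.
3. Acknowledge what this does not protect: the 24-hour rating and guess still follow the message, and the assistant still sees any bleeding.
4. For patients already treated, report bleeding by arm and against the guesses. Use the practitioner questionnaire together with the adverse-event records, since bleeding first seen at the assistant's check may be absent from the questionnaire.
5. Label any analysis of the primary outcome by bleeding as exploratory. Bleeding arises after randomisation and is expected in one arm only, so excluding or adjusting for those who bled can itself distort the comparison.

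The cost is a change in script order and one added table. Patients hear of a bruise a few minutes later, and the procedure differs slightly between earlier and later patients. The gain is confined to patients not yet treated: the article appeared in July 2014, in a trial running from January 2011 to March 2015.
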